### Statistical Analysis Plan

Clinical data will be analyzed with SPSS 24.0 software (SPSS Inc, Chicago, IL, USA). Continuous variables will be presented as mean and SD or as median and interquartile if they are not normally distributed. The baseline variables will be analyzed by the independent-samples t-test and Mann–Whitney U test, where appropriate. Categorical data will be presented as percentages. We will use the mixed-effects model to compare the effect of acupuncture vs. sham acupuncture on blood pressure from baseline to 4 and 8 weeks. The fixed effects are treatment arm, time, group^*^time interaction, and baseline outcome. For metabolomics data, the multivariate and univariate analysis will be performed in combination to determine the plasma metabolites that distinguish EH patients from a healthy subjects, and metabolites that exhibit significant changes before and after treatment in each treatment arm. We will use the Partial least square discriminant analysis (PLS-DA) in SIMCA-P (version 14.0; Umetrics, Umeå, Sweden) and the MetaboAnalyst (http://www.metaboanalyst.ca/MetaboAnalyst/) to fulfill the identification of differential metabolites between groups. All statistical tests will be two-sided, and statistical significance will be set at 5%.

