### Sample Collection and Preservation

We will collect fasting serum and urine samples before acupuncture treatment and on the second day of the final treatment from 8:00–9:00 a.m. We will also collect biospecimens from healthy subjects. Participants are required to (1) be free from the intake of alcohol, refresher drinks, coffee, amino acids, hormone, and vitamin supplements 48 h before sampling, (2) and maintain a regular diet and sleep habits, (3) avoid strenuous exercise 24 h before sampling; and (4) be fasting for 12 h before sampling. Fasting blood samples will be collected into vacutainer tubes with a coagulant; meanwhile, urine samples will be collected in a urinal cup. Both blood and urine samples will be immediately cooled to 4°C. Then these samples will be centrifuged within 2 h at 1500 rpm for 15 min. When completed, serum and urine samples will be separated and transferred to new vials. These samples will be finally stored frozen (−80°C) until metabolomic analysis preparation.

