### Sample Size

According to preliminary data from our pilot study, acupuncture was associated with a 9.6-mmHg (δ) greater reduction of 24-h average systolic blood pressure and a 7.7-mmHg greater reduction of 24-h average diastolic blood pressure as compared with sham acupuncture. Conservatively, we hypothesized that acupuncture is associated with a 7.5 mmHg reduction (σ) in 24-h systolic blood pressure compared to sham acupuncture. The significance level was set at 0.05 (α = 0.05, *Z*_α_ = 1.96), and the power of the test was set at 0.9 (1-β = 0.9, *Z*_1−β_ = 1.28). A total of 64 participants will be required in this study (32 in each group), including compensation for an anticipated dropout rate of 20%. Additionally, 10 healthy participants will be recruited as the healthy control group.

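### The before-after metabolite question rests on paired samples, but no paired method is stated, and the only method named, ordinary PLS-DA, ignores the pairing if it is used for that question

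*Protocol article*

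**What the plan says.** The Statistical Analysis Plan section of the protocol article sets two metabolomics questions. The first is which metabolites separate hypertensive patients from healthy subjects. The second is to find "metabolites that exhibit significant changes before and after treatment in each treatment arm". For both, it says that "the multivariate and univariate analysis will be performed in combination". The next sentence names the method: "We will use the Partial least square discriminant analysis (PLS-DA) in SIMCA-P", together with MetaboAnalyst, "to fulfill the identification of differential metabolites between groups". The univariate test is not named. The mixed-effects model in the same section is described for blood pressure only.

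The Sample Collection and Preservation section places the two samplings "before acupuncture treatment and on the second day of the final treatment". Table 1 agrees, with serum and urine metabolites at week 0 and week 4. The Metabolomics Analysis section describes targeted and non-targeted workflows and adds no paired method.

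**The concern.** The two questions have different data structures. Patients and healthy subjects are independent samples, and ordinary PLS-DA suits that comparison. The before-after question uses two samples from the same patient. Ordinary PLS-DA has no term for the patient. Given before and after samples as two classes, it treats them as unrelated specimens, and lasting differences between patients count as noise although each patient could serve as their own control.

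The effect of acupuncture on the metabolic profile is aim 4 in the Introduction. With at most 32 patients per arm, a real within-patient change could be missed for a reason that costs almost nothing to remove.

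**Working it through.** **What the text fixes.** The article states no power, effect size or before-after correlation for metabolites, so there is no figure of its own to reproduce. The size below rests on assumptions.

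**Inputs from the article.** 32 patients per arm and 20% dropout (Sample Size): 32 × 0.8 = 25.6, taken as n = 26 completers. Two-sided 5% level (Statistical Analysis Plan).

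**Assumed inputs.** One metabolite shifted by d = 0.5 SD, equal SD at both times, and before-after correlation ρ of 0.2, 0.3, 0.5 or 0.7.

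**Paired t-test.** The SD of the difference, in units of the metabolite SD, is √(2(1−ρ)). The noncentrality is d√n / √(2(1−ρ)), on 25 degrees of freedom, with critical value 2.060. The numerator is 0.5 × √26 = 2.550.

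**Unpaired t-test on the same data.** The test uses the standard error √(2/26) = 0.277, so its expected value is about 0.5/0.277 = 1.80 whatever ρ is. The critical value on 50 degrees of freedom is 2.009. Since 1.80 lies below 2.009, power is below one half at every ρ shown. The true variance of the statistic is about 1−ρ, so power is roughly Φ((1.803 − 2.009)/√(1−ρ)), which falls from 41% at ρ = 0.2 to 35% at ρ = 0.7. Simulation, which lets the pooled SD vary, gives the figures in the table.

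| ρ | √(2(1−ρ)) | paired noncentrality | paired power | unpaired power |
|---|---|---|---|---|
| 0.2 | 1.265 | 2.02 | 49% | 41% |
| 0.3 | 1.183 | 2.15 | 54% | 41% |
| 0.5 | 1.000 | 2.55 | 69% | 40% |
| 0.7 | 0.775 | 3.29 | 88% | 38% |

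At ρ = 0 the two tests are practically equal (41% paired, 42% unpaired), so the loss comes entirely from the correlation. With all 32 patients, unpaired against paired power is 51% against 78% at ρ = 0.5, and 51% against 94% at ρ = 0.7.

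**Under no change.** The unpaired t-test at a nominal 5% rejects in about 3% of runs at ρ = 0.2, 2% at 0.3, under 1% at 0.5 and 0.1% or less at 0.7. The error is conservative and does not create false findings.

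**PLS-DA itself.** The pattern is the same when PLS-DA is tested by permutation. One set of assumptions was 26 patients, 100 features of which 10 shift by 0.4 SD, 2 components, 7-fold cross-validation with whole patients left out, 99 permutations and 100 runs. Separate implementations of this kind gave, for unpaired against multilevel PLS-DA, about 20% against 28% at ρ = 0.2 (one implementation), 19–28% against 45–56% at ρ = 0.5, and 8–28% against 80–86% at ρ = 0.7. The Monte Carlo standard error with 100 runs is up to √(0.25/100) = 5 points, and the spread shows that the exact figures depend on the implementation. The direction did not change.

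**The case against.** The strongest objection is that the article nowhere says the before-after samples will be analysed as independent. PLS-DA is tied to differences between groups, which may mean only patients against healthy subjects, or acupuncture against sham. The univariate analysis could be paired, and a full protocol or analysis plan that is not shown may say so. This stands. A reader might infer that the plan assigns the before-after comparison to PLS-DA and so discards the pairing, but no sentence says that.

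It does not dispose of the point. The article chooses to name the method and software, places them directly after the before-after question, and does not limit them to independent samples. If PLS-DA is meant for both questions, it fits the second badly. If it is meant only for independent groups, the before-after question has no named multivariate method although one is promised. A paired univariate test would not repair an unpaired multivariate half, since the two are to be used together.

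A second objection also stands: the contrast between arms does not need per-patient change to be valid. Post-treatment samples from randomised arms are independent and can be compared directly.

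Third, the trial is meant to give preliminary data and promises no power for metabolomics, and the primary blood pressure outcome is untouched. That limits the weight of the point. It does not affect whether paired samples should be analysed as paired.

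**Conclusion.** The point holds in conditional form. The before-after samples are paired, ordinary PLS-DA is the only method named, and no paired method is stated. If PLS-DA is applied to before and after samples as two classes, power is lost when the before-after correlation is positive.

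For one metabolite with a 0.5 SD shift and 26 completers, the loss runs from about 8 percentage points at a correlation of 0.2 (49 − 41) to about 50 at 0.7 (88 − 38). Correlation, shift and number of completers are assumptions, and only the last derives from the article's own figures. A single dramatic figure, such as a fall from 80% to 28%, comes from one assumed correlation of 0.7 in one simulation and should not be read as the size of the problem. The documents also do not support a claim that aim 4 cannot be answered.

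**What to change.** In the Statistical Analysis Plan section, separate the questions by data structure.

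- **Before-after within each arm, multivariate:** multilevel PLS-DA, on data centred within each patient or on after-minus-before differences. Validate it by swapping before and after labels within patients and by leaving out whole patients.
- **Before-after, single metabolites:** paired tests, or a mixed model with a patient random effect.
- **Independent samples (patients against healthy subjects, acupuncture against sham):** ordinary PLS-DA may stay. Between arms, per-patient change or baseline adjustment can add precision but is not needed for validity.

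The cost is wording and one preprocessing step. No new samples or visits are needed. The downside is that patients with only one of the two samples drop out of the multilevel PLS-DA, although they can stay in the mixed model.

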## Abstract

Essential hypertension is a polygenic cardiovascular disease that is associated with maladaptive metabolic changes. Acupuncture as a non-pharmacologic intervention is used to lower blood pressure and improve metabolic dysfunction. However, such effects have not been clinically characterized. We will conduct a randomized clinical trial to evaluate the antihypertensive effect of acupuncture among patients with essential hypertension and determine the associated metabolic improvements. This study is a phase II, two-arm, randomized, sham-controlled trial (Trial registration: ChiCTR2100043737), in which biospecimens will be collected for metabolic profiling. A total of 64 patients with a clinical diagnosis of essential hypertension will be randomly assigned to either the acupuncture or the sham acupuncture group in a 1:1 ratio. All participants will receive 10 treatments over 4 weeks, with three sessions per week for the first 2 weeks and two sessions per week for the remaining weeks. The primary outcome is the change of the systolic and diastolic blood pressure measured by the 24-h ambulatory blood pressure monitoring from baseline to 4 weeks. Secondary outcomes include the circadian rhythm of blood pressure, sleep quality measured by the Insomnia Severity Index, cognitive function measured by the Montreal Cognitive Assessment, and others. Fasting blood serum and urine samples will be collected at baseline and 4 weeks for targeted and untargeted metabolomics analysis. We will use the mixed-effects model and other related bioinformatics approaches to analyze the clinical and metabolome data. This metabolomic-based trial will provide important clinical data regarding the efficacy of acupuncture for essential hypertension to better inform evidence-based care delivery for hypertension patients. Moreover, the findings will offer important insights into the mechanism of action of acupuncture for hypertension by revealing its effect on metabolism. The results of this study will be used to inform the design of a statistically powered, multicenter, randomized trial. We will publish the study findings in peer-reviewed journals. The ethical approval of this study has been reviewed and approved by the Sichuan Regional Ethics Review Committee on Traditional Chinese Medicine (ID: 2021KL-006). The outcomes of the trial will be disseminated through peer-reviewed publications.

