Our pilot studies highlighted that the antihypertensive effect of acupuncture was associated with metabolic improvements in EH patients, possibly through modulating fatty acid metabolism and the citric acid cycle (23–25). Building on these preliminary findings, we conducted a hybrid clinical trial among patients with EH to (1) assess the efficacy and safety of acupuncture vs. sham acupuncture on the reduction of blood pressure, (2) evaluate the effect of acupuncture on EH-related sleep and cognitive symptoms and the quality of life, (3) explore potential clinical factors that are predictive of treatment response to acupuncture such as treatment expectancy, sex dimorphism, traditional Chinese medicine body constitution (TCMBC), and (4) investigate the effect of acupuncture on the targeted and untargeted metabolic profile.

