#### Acupuncture Intervention

Patients in the acupuncture group will receive electroacupuncture treatment. Sterile disposable acupuncture needles (0.18 × 25 mm, 0.18 × 30 mm; Zhongyan Taihe Medical Instrument Co., Ltd., Beijing, China) will be used for treatment. The manipulations are as follows: Acupuncture needles will be inserted into acupoints at a depth of 20-25 mm after skin disinfection using an alcohol wipe. After insertion, needles will be manually manipulated by gentle lifting, thrusting, and rotating until to achieve the *de-qi* sensation. We will use Hwato therapeutic apparatus (Hwato SDZ-II Acupoint Nerve Stimulator, Suzhou Medical Co., Ltd.) to connect the needles at the two acupoints located in the ipsilateral limb. The frequency will be 60/100 Hz, and the electric current will vary from 1.0 to 2.0 mA until the patients feel comfortable. The acupuncture needles will be retained for 25 min in each session. In addition, all participants will receive lifestyle education on how to improve blood pressure through diet, weight control, and exercise.

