## Discussions

Acupuncture reduces stress and is widely used as a non-pharmacological treatment for cardiovascular diseases and metabolic disorders (20, 47). However, the modulating effects of acupuncture on the cardiovascular and metabolic systems are not well understood so far. Here, we present the design and methodology of our ongoing randomized clinical trial which evaluates the efficacy and safety of acupuncture vs. sham acupuncture on blood pressure and metabolic profile among patients with EH. We will enroll 64 eligible patients and measure their blood pressure with the 24-h ABPM test after administrating 10 acupuncture sessions over 4 weeks. Meanwhile, we will determine the changes in the metabolic profile associated with the treatment effect, via targeted and untargeted metabolic profiling. Additionally, we will identify potential clinical variables and metabolic signatures that are predictive of treatment response to acupuncture among patients with EH. The study findings may have important clinical and research implications.

Till now, the role of acupuncture in blood pressure management remains unclear. Our previous systematic review of randomized clinical trials found inconsistent results concerning the effect of true vs. sham acupuncture on blood pressure, due to the risk of bias associated with sample size, control arms, and treatment population (16, 20, 48). Further, our understanding of the biological foundation of acupuncture is limited, especially in terms of cardiovascular and metabolic modulation. Although metabolic dysregulation has been closely linked to the pathogenesis of EH (49–51), fewer studies have been conducted to assess the metabolic changes in the non-pharmacological blood pressure treatment (23). Our study incorporates metabolomics technology in the design of a rigorous randomized control trial to characterize the metabolic signatures associated with changes in clinical outcomes. This study will provide preliminary data to support the design of a sufficiently powered, randomized controlled trial in the future, which will provide important clinical data to inform the non-pharmacologic management of EH, and physiological information to understand the biological underpinnings of acupuncture for blood pressure and metabolism regulations.

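### The only treatment-related metabolite analysis spelled out is before-after change within each arm, although the aim is the effect of acupuncture against sham

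*Protocol article*

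**What the plan says.** The Introduction's fourth aim is to "investigate the effect of acupuncture on the targeted and untargeted metabolic profile". The Discussions section states the comparison behind it: the trial "evaluates the efficacy and safety of acupuncture vs. sham acupuncture on blood pressure and metabolic profile among patients with EH".

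The Statistical Analysis Plan section gives the metabolomic analysis two targets. One is "to determine the plasma metabolites that distinguish EH patients from a healthy subjects". The other is "metabolites that exhibit significant changes before and after treatment in each treatment arm". It then names PLS-DA and MetaboAnalyst as tools "to fulfill the identification of differential metabolites between groups", without saying which groups are meant.

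The same section does specify a between-arm model, but for another outcome: "We will use the mixed-effects model to compare the effect of acupuncture vs. sham acupuncture on blood pressure from baseline to 4 and 8 weeks". Its fixed effects are arm, time, their interaction and the baseline value. The Abstract is looser: "We will use the mixed-effects model and other related bioinformatics approaches to analyze the clinical and metabolome data".

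On co-intervention, the Acupuncture Intervention section says that "all participants will receive lifestyle education on how to improve blood pressure through diet, weight control, and exercise", and the Sham Acupuncture Intervention section confirms that sham patients get the same education. Serum and urine are sampled at baseline and week 4 (Abstract; Table 1).

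**The concern.** The aim is causal, and the sham arm is there to support it. A before-after test within one arm does not use that control. It asks whether a metabolite moved, not whether it moved more under acupuncture than under sham.

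This matters here because both arms are taught about diet, weight and exercise, which can plausibly change metabolites. Anything else that acts on both arms over four weeks has the same effect. Comparing two lists of within-arm findings does not repair this: significance in one arm and not in the other is not a test of a difference between them. A mechanistic claim built on such lists could attribute to needling what belongs to education or time.

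**Working it through.** **Step 1: what each named analysis can answer.**

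| Analysis in the Statistical Analysis Plan section | Contrast | Answers acupuncture against sham on metabolites? |
|---|---|---|
| Hypertensive patients against healthy subjects | not randomized | no |
| Change in each arm | before against after, one arm at a time | no |
| Mixed model with arm-by-time term | acupuncture against sham | assigned to blood pressure only |
| PLS-DA and MetaboAnalyst | groups not defined | not stated |

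No row states a randomized comparison of metabolite change.

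**Step 2: how far within-arm testing can mislead.** The article gives no figure to reproduce here, so this is an illustration.

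Inputs:
- Two-sided 5% tests (Statistical Analysis Plan).
- 32 patients per arm and 20% dropout (Sample Size): 32 × 0.8 = 25.6, taken as 26 completers per arm.
- An identical true change in both arms, so that acupuncture adds nothing. Its size e, in SDs of the change, is assumed.

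Formulas, for n per arm:
- p = P(|T| > t*), where T is noncentral t with n − 1 degrees of freedom and noncentrality e√n, and t* is the 0.975 quantile of central t. This is the chance that the paired test is significant in one arm.
- The arms are independent, so P(significant with acupuncture only) = p(1 − p).

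Example, n = 26 and e = 0.4: noncentrality 0.4 × √26 = 2.04, p = 0.500, and p(1 − p) = 0.500 × 0.500 = 0.250.

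| Shared change e | p, n = 26 | Acupuncture only, n = 26 | p, n = 32 | Acupuncture only, n = 32 |
|---|---|---|---|---|
| 0 | 0.050 | 0.048 | 0.050 | 0.048 |
| 0.2 | 0.165 | 0.138 | 0.195 | 0.157 |
| 0.3 | 0.313 | 0.215 | 0.376 | 0.235 |
| 0.4 | 0.500 | 0.250 | 0.592 | 0.242 |
| 0.5 | 0.688 | 0.215 | 0.782 | 0.170 |
| 0.6 | 0.836 | 0.137 | 0.908 | 0.084 |

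A two-sample test of the changes keeps a 5% error rate in every row, because the true difference between arms is zero.

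**Step 3: check by simulation.** With 100,000 simulated trials at n = 26 and e = 0.4, acupuncture was significant in 50.4%, acupuncture alone in 25.1%, and the direct between-arm test in 5.1%.

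**The case against.** The strongest reply is that a between-arm analysis is already implied. The Abstract mentions the mixed model together with the metabolome data, and the only mixed model the article describes is a baseline-adjusted comparison of arms. The article often uses the word group for the allocated arms, including in the interaction term, so the PLS-DA sentence may cover acupuncture against sham. A condensed article also need not give model detail.

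Part of this stands. These sentences leave room for the randomized contrast, so a reader who infers that the plan excludes it goes too far. They do not state it, however. The Abstract joins the model with unspecified bioinformatics methods, and the analysis section assigns the model to blood pressure. The word group also covers the healthy controls. Nor is this merely missing detail: the article did choose a treatment-related target, and it is the within-arm one.

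Three further inferences are tempting and unsupported:

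- *That the trial will credit acupuncture with whatever is significant in that arm alone.* No such decision rule is written. The tests make that misreading possible; they do not prescribe it.
- *That half of all metabolites would be significant in exactly one arm.* That figure, 2 × 0.25 = 0.50, requires every metabolite to shift by 0.4 SD in both arms with 26 per arm. Power is then 50%, where 2p(1 − p) is at its maximum.
- *That regression to the mean inflates the metabolite changes.* Patients are selected mainly on blood pressure, and the documents give no mechanism by which this would carry over to metabolites.

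It is also fair to say that metabolites are neither the primary outcome nor in the secondary list under Study Design, and that the trial is meant to provide preliminary data.

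**Conclusion.** The point holds, at moderate severity. The one treatment-related metabolite target that the plan spells out would not answer its own aim, and the sentences hinting at a between-arm analysis do not specify one.

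If both arms shift equally by 0.2 to 0.5 SD, within-arm testing finds a metabolite significant with acupuncture only in 14% to 25% of cases at 26 per arm, and in 16% to 24% if all 32 complete. A direct comparison gives 5%. The 25% is a worst case. With no shared shift the acupuncture-only rate is 4.8%, so the problem depends on education or time actually moving metabolites. The shift sizes are assumptions, and the percentages measure a possible reading of two within-arm results, not a rule in the plan. The primary blood-pressure comparison is unaffected.

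**What to change.** State in the Statistical Analysis Plan section that the main treatment-effect analysis for metabolites is the randomized acupuncture-versus-sham comparison at week 4, adjusted for baseline abundance. Either of two models would serve:

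- week-4 log abundance regressed on arm and baseline log abundance; or
- the arm-by-time model already described for blood pressure, fitted to each metabolite.

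Report the arm difference with its confidence interval. Keep the order in the Metabolomics Analysis section: the targeted panel first (Krebs-cycle metabolites and those from the earlier studies), then the untargeted features. Define which groups the PLS-DA compares, and label within-arm changes as descriptive.

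This needs a few sentences and modest programming. No new samples are required, since both arms are already sampled at baseline and week 4. The drawback is that fewer metabolites will probably be called significant: with equal arms, a difference between two changes has a standard error √2 times that of one arm's change, and shared shifts no longer count as findings. The wording should be settled before unblinding, so that the contrast is not chosen after the results are seen.

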### Study Design

This study is a randomized controlled trial conducted at the Chengdu University of Traditional Chinese Medicine and the Geriatric Hospital of Sichuan Province, Chengdu, China. A total of 64 patients with essential hypertension and 10 healthy subjects will be recruited. 64 patients will be randomly allocated in a 1:1 ratio to either the acupuncture or sham acupuncture group. Patients will receive 10 treatments over 4 weeks. The primary outcome is the 24-h average blood pressure measured with 24-h blood pressure monitoring (24-h ABPM) at 4 weeks. Secondary outcomes include blood pressure measured at 8 weeks, the 24-h circadian rhythm of blood pressure, the sleep quality measured by the Insomnia Severity Index (ISI), cognitive function measured by the Montreal Cognitive Assessment (MoCA), TCMBC, health-related quality of life, patient's treatment expectancy, and adverse events. The details of the study design are shown in Figure 1. The timeline of recruitment, interventions, and outcome measurements is shown in Table 1.

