### Metabolomics Analysis

Serum samples will be pre-processed, divided for the available targeted and non-targeted metabolomics methods, and dried. Samples will then be reconstituted and analyzed using metabolomic platforms. The preliminary targeted analysis will consist of mining for metabolites in the Krebs Cycle and others identified in previous studies (23–25). Secondary analysis will leverage non-targeted (differential features analysis) workflows of the entire LC-MS/GC-MS datasets through a combination of the vendor, open source, and commercial software tools, followed by a metabolite identification pipeline to identify statistically important features.

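### Untargeted metabolomics: PLS-DA plus unadjusted 5% tests identifies differential metabolites, with no conclusion tied to validated performance

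*Protocol article*

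**What the plan says.** All of this is in the protocol article.

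- **Method and purpose (Statistical Analysis Plan).** "We will use the Partial least square discriminant analysis (PLS-DA) in SIMCA-P (version 14.0; Umetrics, Umeå, Sweden) and the MetaboAnalyst" are named as the tools "to fulfill the identification of differential metabolites between groups". PLS-DA is the only multivariate method named. The section also says that "the multivariate and univariate analysis will be performed in combination". The targets are metabolites that separate patients from healthy subjects, and metabolites that change from before to after treatment within each arm.
- **Decision level (same section).** "All statistical tests will be two-sided, and statistical significance will be set at 5" per cent. No adjustment for the number of metabolites is stated.
- **Data (Metabolomics Analysis).** A targeted analysis of Krebs-cycle and previously identified metabolites comes first. A secondary analysis then uses "non-targeted (differential features analysis) workflows of the entire LC-MS/GC-MS datasets". Neither feature count is given.
- **Sample sizes (Study Design, Sample Size).** "64 patients will be randomly allocated in a 1:1 ratio to either the acupuncture or sham acupuncture group". That is 32 per arm with 20% dropout allowed for. "Additionally, 10 healthy participants will be recruited as the healthy control group".

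The article states no cross-validation, permutation test or selection cut-off for the metabolomics. It also does not say that fitted separation will be taken as evidence, or that validation will be left out.

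**The concern.** PLS-DA is supervised: it uses the group labels to build the axes on which the groups are then shown apart. With many more features than samples, some combination of features will separate almost any labelling. Fitted separation then says little about whether the groups differ.

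The univariate step looks like a safeguard but is not an independent one. A feature ranks high in PLS-DA because it covaries with the label, and the t-test measures the same thing. At an unadjusted 5% level, about one null feature in twenty passes both.

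At stake is the fourth aim in the Introduction, the effect of acupuncture on the metabolic profile. Followed as written on untargeted data, the rule returns a list of differential metabolites for patients v healthy subjects and for before v after in each arm, sham included, even if nothing differs. A list from the sham arm could be read as a biological effect of sham treatment.

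**Working it through.** The plan gives no error rate or sample-size figure for the metabolomics, so there is none to reproduce. Its 64 patients are sized on blood pressure.

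**Inputs from the article.** 64 patients, 10 healthy subjects, 32 per arm, 20% dropout, two-sided 5%. Completers per arm: 32 × (1 − 0.20) = 25.6, about 26.

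**Assumptions.** 20 to 3,000 features, two PLS components, autoscaled data, 7-fold cross-validation, and VIP > 1 as the importance cut-off. None of these is in the article.

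**Formulas.** With y the group label and ŷ the prediction:
- R2Y = 1 − Σ(y − ŷ)² / Σ(y − ȳ)², with ŷ fitted. Q2 is the same with ŷ cross-validated.
- VIP_j = √(p · Σ_a w_ja² SS_a / Σ_a SS_a), where p is the number of features, w_ja the weight of feature j on component a, and SS_a the label variation that component a explains. Each component's squared weights sum to 1, so the mean of VIP² is always 1. VIP > 1 is therefore a relative cut-off that flags features whether or not any signal exists.

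**Result with no true difference** (independent normal features, 200 runs per row):

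| Groups | Features | R2Y | Fitted AUC | Perfect separation | Cross-validated AUC | Q2 > 0 | VIP > 1 and p < 0.05 | At least one such feature |
|---|---|---|---|---|---|---|---|---|
| 64 v 10 | 20 | 0.26 | 0.887 | 0% | 0.50 | 1.5% | 5.0% | 66% |
| 64 v 10 | 50 | 0.54 | 0.986 | 10% | 0.49 | 0.5% | 4.9% | 94% |
| 64 v 10 | 200 | 0.92 | 1.000 | 100% | 0.51 | 6.0% | 5.0% | 100% |
| 64 v 10 | 1,000 | 1.00 | 1.000 | 100% | 0.50 | 21.5% | 5.0% | 100% |
| 26 v 26 | 20 | 0.35 | 0.844 | 0% | 0.48 | 0.5% | 4.2% | 58% |
| 26 v 26 | 50 | 0.67 | 0.975 | 6% | 0.51 | 2.5% | 5.0% | 91% |
| 26 v 26 | 200 | 0.95 | 1.000 | 100% | 0.50 | 14.5% | 5.1% | 100% |
| 26 v 26 | 1,000 | 1.00 | 1.000 | 100% | 0.51 | 34.5% | 5.0% | 100% |

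32 v 32 and 3,000 features follow the same pattern.

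**Correlated features** (10 latent factors carrying half the variance). Fitted AUC of at least 0.95 occurs in 71%, 100% and 100% of null datasets for 64 v 10 at 50, 200 and 1,000 features, and in 25%, 100% and 100% for 26 v 26. Cross-validated AUC stays at 0.48 to 0.50. At 20 features the share is 0 to 8%.

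**Paired before/after samples** (within-patient correlation assumed 0.5). The share is 65% at 200 features and 92% at 1,000, and it falls as pairs are added.

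**False metabolites.** The expected number is 0.05 × p: 1 of 20, 10 of 200, 50 of 1,000. For independent features the chance of at least one is 1 − 0.95^p, which is 64% at 20 and 92% at 50, in line with the table. The share passing VIP > 1 and p < 0.05 equals the share passing p < 0.05 alone, so PLS-DA removes almost none of these and adds none.

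**Does validation repair it?** A label-permutation test of cross-validated error at 32 v 32 with 200 features (60 runs, 59 permutations) rejected in 5% of null runs. With 10 truly shifted features it rejected in 53% of runs (shift 0.6 SD) and 100% (shift 1.0 SD). In correlated null data at 64 v 10 and 26 v 26, a permutation gate passed about 3 to 8%. A bare Q2 > 0 rule is not enough: at 1,000 or more features it is met in 22% to 40% of null runs.

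**The case against.** The strongest reply is that this is an omission in a condensed article. Folds, permutation counts and importance cut-offs commonly sit in a full plan, which is not shown here. That stands as far as it goes: their absence from the article does not prove that they are missing. What the article does state is an identification rule with a decision level of 5%, and that rule, as stated, lets false metabolites through.

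Two stronger readings are tempting and are not supported:

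- **That PLS-DA cannot tell a signature from noise.** The permutation results show that it can once validated. The fault lies only in reading the fitted model unvalidated.
- **That the plan accepts fitted separation as evidence.** The article does not say so. It also combines PLS-DA with univariate tests, so the 38–39% of correlated null features (32–36% of independent ones) that VIP > 1 alone would flag is not the plan's false-positive rate. Under the stated combination that rate is about 5%, and it comes from the unadjusted tests.

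Three further points limit the scope. The separation artefact is small in a targeted panel of about 20 metabolites, which the article analyses first. Pairing weakens it for before/after comparisons. Metabolomics is one of four aims, outside the primary outcome, in a phase II trial. The signatures of treatment response in the Discussions are a separate prediction question to which the Statistical Analysis Plan does not assign PLS-DA.

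**Conclusion.** The point holds for the untargeted data. With hundreds of features, fitted separation of 64 v 10, or of 26 to 32 independent samples per group, occurs in essentially all datasets with no difference. For paired before/after samples it occurs in most (65% to 92% in the setting checked). Adding p < 0.05 leaves about 5% of null features flagged, so neither step protects against a false signature.

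This rests on assumed values for feature count, correlation structure, two components and VIP > 1. The 5% figure for before/after also assumes a paired test, which the article does not specify. A small panel escapes most of the separation artefact but not the unadjusted 5% level. The matter should be settled before the metabolomics is analysed; it does not touch the blood pressure outcome.

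**What to change.** In the Statistical Analysis Plan section, add:

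1. A PLS-DA model is interpreted only if its cross-validated Q2 or AUC beats a label-permutation distribution at 5%. All samples of one patient stay in the same fold, and labels are permuted within patient for before/after comparisons. Otherwise no multivariate signature is claimed for that comparison.
2. PLS-DA only ranks metabolites. A metabolite is declared differential only from a univariate test with false-discovery control across the features of that comparison, paired for before/after.

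If the full plan already holds such a rule, one clause citing it is enough. A PCA plot beside each PLS-DA plot and the exact number of permutations are optional.

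The cost is a few sentences and a little computing, with no new patients or samples. The downside is that some comparisons may end with no reportable signature.
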